### Setting and intervention

2.4

Coagulation tests will be performed according to standard clinical procedures. To minimize interindividual variability, all participants’ blood samples will be analyzed both after manual transport and after automated transport via PTS. Each participant serves as their own control. To avoid artifacts that could arise from transferring a portion of the blood from one sample tube into another (e.g., shear forces or bubble formation due to incomplete tube filling), which does not reflect clinical reality, separate blood samples will be drawn for PTS and manual transport for all participants. Blood samples will be collected simultaneously for each participant, and the transport modality (manual or PTS) for specific samples will be randomized. To address these two research questions, blood samples will be analyzed after manual transport and after pneumatic tube transport. During transport, speed and acceleration are continuously recorded by a data logger (accelerometer, Figure 2) that is transported along with the blood sample. This enables the assessment of the variability of the acceleration forces within the PTS, despite the constant nominal speed and identical transport routes. Since blood samples are transported at different times and days, variations in PTS utilization and transport dynamics (e.g., delays, intermittent stops) naturally occur, which introduces random variations in the forces acting during transport. Additionally, alternative speeds will be programmed within the PTS to introduce controlled variations in acceleration forces to investigate the threshold at which PTS forces affect coagulation analyses. There are also two possible pathways between the ICU and the central laboratory in the study center once more variations are generated. To conclude, the following systematic variations in PTS transport conditions will be implemented in the VETaPT trial: 1. High vs. low transport speed by adjusting the PTS compressor settings; 2. Transport of blood samples in a small transport bag vs. in a specific insert that fixates the samples within the PTS container. The decision regarding the use of the insert or a bag as well as the speed settings is made randomly before the start of automated transport. This will further increase the variability of the AUC value as a parameter of the applied accelerations.

**Figure 2 fig2:**
[figure not shown]
Data logger. This three-axis accelerometer (MSR 145, MSR Electronics, Switzerland) enables the measurement of acceleration along three spatial axes with a sampling rate of 1 kHz, storing the highest recorded value at 50 Hz. Owing to its lightweight and miniaturized design, the sensor can be easily transported within the PTS, and acceleration forces can be continuously monitored during PTS transport.

For five participants, a vibration exciter (LDS Permanent Magnet Vibration System, V455 Series, Hottinger Brüel & KJÆR GmbH) will be used to generate controlled acceleration forces, allowing precise evaluation of their effect on coagulation results. Unlike the PTS, which produces varying acceleration magnitudes, the vibration exciter enables precise and reproducible acceleration forces. This approach is expected to provide more precise insights into which components of the AUC may have a disproportionately high impact on possible changes in the test results.

### Relevance for critically ill septic patients

2.5

Septic patients often exhibit altered coagulation profiles (4, 5, 27), making it uncertain whether findings from healthy volunteers can be directly extrapolated to this population. Since it is unknown whether the known coagulation system alterations described in critically ill patients influence their susceptibility to PTS-induced forces, the VETaPT trial will include both healthy volunteers and critically ill septic patients. Furthermore, since critically ill patients often require rapid laboratory diagnostics, it is particularly important to investigate potential PTS transport effects in this group. During routine clinical blood sampling, additional blood samples will be collected for study purposes. These will be analyzed after both manual and PTS transport, ensuring that each patient serves as their own control.

### Quantifying acceleration forces

2.6

During transport, speed and acceleration are continuously recorded via a data logger. For this purpose, a three-axis accelerometer (MSR 145, MSR Electronics, Switzerland) (Figure 2) will be transported alongside the sample. This enables the measurement of acceleration along three spatial axes with a sampling rate of 1 kHz, storing the highest recorded value at 50 Hz. Owing to its lightweight and miniaturized design, the sensor can be easily transported within the PTS. The digital analysis of recorded data allows visualization of acceleration throughout transport (Figure 3A). The forces acting during transport can be graphically represented as the area under the curve (AUC) value for each transport instance (Figure 3C). Specifically, acceleration during transport is quantified by calculating the AUC, with a modification to the approach of Streichert et al. (28). This involves classifying absolute vector values into bins, similar to a histogram (Figure 3B), as described by Streichert et al. (28). The values exceeding a predefined acceleration threshold are subsequently summed (cutoff in Figure 3C). The threshold acceleration is defined as the typical acceleration occurring during manual transport. In contrast to Streichert et al. (28), the AUC calculation in the VETaPT trial involves dividing the result by the accelerometer’s sampling rate. This adjustment ensures generalizability, as otherwise, the AUC would be dependent on the sampling rate of the accelerometer. The AUC is calculated as follows:

$$\mathrm{AUC}=\frac{1}{f}*\sum_{i_{0}}n_{i}*\frac{\left(a_{u,i}+a_{l,i}\right)}{2}$$

where f represents the accelerometer sampling rate and where i_0_ denotes the index of the first bin exceeding the acceleration threshold. Within the sum operator, for each bin i, the product of the number of counts (n_i_) and its mean acceleration, which is calculated as the mean of the upper (a_u,i_) and lower (a_l,i_) bin edges, are multiplied. The formula provided above yields results equivalent to numerically integrating the pure acceleration curve (Figure 3A) while considering only accelerations exceeding the chosen threshold. This approach enables the correlation of differences in coagulation test results between transport methods with their respective AUC values. Consequently, the assumed relationship between acceleration forces and coagulation test results should become evident across different acceleration levels and PTS compressor settings. This method replaces the commonly used yet imprecise characterization of acting forces on the basis of average transport speed with a more methodologically robust and physically accurate approach. By doing so, the acceleration forces—one of the key parameters influencing coagulation activation—are quantified in a standardized and comparable manner. The measured AUC value thereby serves as a parameter that captures the total magnitude of forces exerted by the PTS.

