**Figure 3 fig3:**
[figure not shown]
Quantification of acceleration forces during pneumatic tube transport. **(A–C)** Illustrates the quantification of acceleration forces for one transport process via an area under the curve (AUC)-based method. Digital analysis of the recorded data from the data logger enables visualization of acceleration over the transport duration **(A)**. In the next step, the absolute vector values are categorized into bins, similar to a histogram **(B)**. The number of bins has been decreased for illustration purposes. The values exceeding a predefined acceleration threshold, defined as the typical acceleration occurring during manual transport, are subsequently summed **(C)**. This approach allows the forces acting during transport to be graphically represented as the AUC value for each transport instance **(C)**.

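### The AUC formula counts stored 50 Hz peak values but divides by the sampling rate, stated as 1 kHz; it is not the claimed integral under either reading of f, so any exported threshold depends on the logger mode

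*Protocol article*

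**What the plan says.** All of this is in the protocol article, section 2.6 (Quantifying acceleration forces); the Figure 2 legend repeats the logger specification.

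- **Logger:** it measures three axes "with a sampling rate of 1 kHz, storing the highest recorded value at 50 Hz".
- **What is counted:** the sum runs over bins and uses "the product of the number of counts (n_i_) and its mean acceleration". The Figure 3 legend describes the input: "Digital analysis of the recorded data from the data logger enables visualization of acceleration over the transport duration".
- **Divisor:** "the AUC calculation in the VETaPT trial involves dividing the result by the accelerometer’s sampling rate", and under the formula, "where f represents the accelerometer sampling rate".
- **On dependence on the logger rate:** "This adjustment ensures generalizability, as otherwise, the AUC would be dependent on the sampling rate of the accelerometer".
- **On equivalence to integration:** above the cut-off, the formula "yields results equivalent to numerically integrating the pure acceleration curve".

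Section 2.1 relies on this scale. As a secondary objective it seeks a force threshold that other tube systems could apply from accelerometer data alone. Section 2.7.7 enters the AUC as an independent variable in the logistic regression.

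**The concern.** Only stored values can be binned, so the counts accrue at 50 per second. The divisor is described as the sampling rate, which the same section gives as 1 kHz. The section never ties f to 50 Hz. It states that the highest value is kept, but does not consider what this does to the sum.

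A sum of counts times acceleration becomes a time integral only if two things hold: the divisor is the rate of the values counted, and each value represents its time slot. The first fails if f = 1 kHz. The second fails in either case, because each 20 ms slot is represented by its maximum.

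At stake is the threshold. Another hospital would compare its own AUC with a published number. If it reads f differently, or runs a logger with another storage rate or without peak-hold, the two numbers are not on the same scale.

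**Working it through.** **Inputs (section 2.6):** sampling 1000 Hz; storage 50 Hz, highest value kept; ratio 1000/50 = 20 samples per stored value. The document gives no numeric AUC and no numeric cut-off, so there is no stated figure to reproduce.

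**1. Bounds, with no waveform assumed.** In each 20 ms window let S be the sum of the 20 acceleration magnitudes (those below the cut-off set to zero) and M the largest of them. Since the values are non-negative, M ≤ S ≤ 20M. Bin-midpoint rounding is ignored.

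- 1 kHz integral: ΣS/1000.
- Formula with f = 1000: ΣM/1000. Ratio to the integral: ΣM/ΣS, between 1/20 = 0.05 and 1.
- Formula with f = 50: ΣM/50. Ratio to the integral: 20·ΣM/ΣS, between 1 and 20.
- The two readings of f differ by exactly 1000/50 = 20.

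**2. The two extremes, for one window with peak height h.**

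| Window content | 1 kHz integral | f = 1000 | f = 50 |
|---|---|---|---|
| constant h for 20 ms | 20h/1000 = h/50 | h/1000 (0.05×) | h/50 (1×) |
| single 1 ms spike of h | h/1000 | h/1000 (1×) | h/50 (20×) |

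Both windows leave the same stored record, h. No choice of f can be right for both.

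**3. Illustration.** Simulated 60 s three-axis signals at 1 kHz; waveforms and cut-off (arbitrary units) are assumptions. Entries are the ratio to the 1 kHz integral.

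| Signal | Cut-off | f = 1000 | f = 50 |
|---|---|---|---|
| slow motion | 0 / 2 | 0.051 / 0.051 | 1.01 / 1.02 |
| vibration near 25 Hz | 0 / 2 | 0.066 / 0.066 | 1.33 / 1.33 |
| vibration near 100 Hz | 0 / 2 | 0.069 / 0.069 | 1.38 / 1.38 |
| noise | 0 / 2 | 0.094 / 0.096 | 1.88 / 1.93 |
| 5 ms shocks | 0 / 2 | 0.091 / 0.352 | 1.81 / 7.04 |

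**4. Does dividing by the storage rate remove dependence on it?** Peak-hold at 100, 50 and 10 Hz, each divided by its own rate:

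- noise, no cut-off: 1.71, 1.88, 2.23 times the integral;
- shocks, cut-off 2: 3.93, 7.04, 30.70 times (at 10 Hz a window holds 100 samples, so the upper bound there is 100).

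The dependence remains.

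**5. Effect on inference within the trial.** Dividing the covariate by 20 in a simulated logistic regression multiplies the coefficient by 20 (1.2065 to 24.131) and leaves the Wald z at 5.164 in both fits.

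**The case against.** The best defence is that the text itself points to f = 50. The equivalence sentence refers to the curve in Figure 3A, which is drawn from recorded data. If that curve is the stored 50 Hz record, the formula reproduces its integral when f is the storage rate. A reader might infer from the literal wording that the trial's AUC values are, or will be, wrong by a factor of 20. The document does not support that: it reports no AUC, and its own equivalence statement favours the other reading. What stands is that f is defined by a name the text gives only to 1 kHz, and that the stored curve is a peak envelope and not the acceleration curve.

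A reader might also infer that the regression is invalidated. It is not. A constant factor leaves p-values, power and the odds ratio per SD unchanged, and an exposure index need not be an exact integral to predict a change in clotting time.

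Nor is the threshold wholly untransferable. The article discloses the logger model, sampling rate and storage mode, so a site using the same settings stays comparable. Section 2.1 also words the extrapolation cautiously and lists it as secondary.

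Finally, dividing by the record rate does remove the direct proportionality to the number of records. The adjustment is useful, but the sentence claims more than it delivers.

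**Conclusion.** The point holds as a misstatement in the printed formula and in the two claims attached to it. The 0.05 to 1 and 1 to 20 ranges follow from algebra. They assume that the stored value is the largest vector magnitude in each window. The document does not say whether peaks are stored per axis; if absolute peaks were, the vector built from them would be larger still (1.46 against 1.33 in the 25 Hz example).

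The factor of 20 is exact between the two readings of f, but only the extreme against the true integral. The size of the peak-hold excess on real transports is unknown. The simulated ratios show direction and signal dependence only: other assumed waveforms and cut-offs give 1.2 to 9.0 with f = 50. None of them should be quoted as the bias of this trial.

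The harm falls on the absolute threshold and its export. Because the excess varies with the signal, it could also distort comparisons across the speed and bag-versus-insert conditions of section 2.4. The same applies to the vibration-exciter work, which the Discussion intends to separate peak magnitude from continuous exposure. That distortion is possible, not shown.

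**What to change.** In section 2.6:

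1. Define f as the rate of the stored records that are counted, 50 Hz.
2. Name the measure a peak-hold AUC (1 kHz sampling, 20 ms maximum).
3. Delete the equivalence sentence, or limit it to the integral of the stored peak envelope. Delete the rate-independence sentence, or limit it to removing proportionality to the number of records.
4. State the logger settings as part of any reported threshold, and say that it applies to loggers run in the same mode.

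The cost is one definition, one label and two sentences, plus a line wherever a threshold is reported. No new data are needed. Storing raw 1 kHz values and dividing by 1000 would approximate the intended integral. That is optional and depends on a logger capability that the document does not give.

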**Figure 3 fig3:**
[figure not shown]
Quantification of acceleration forces during pneumatic tube transport. **(A–C)** Illustrates the quantification of acceleration forces for one transport process via an area under the curve (AUC)-based method. Digital analysis of the recorded data from the data logger enables visualization of acceleration over the transport duration **(A)**. In the next step, the absolute vector values are categorized into bins, similar to a histogram **(B)**. The number of bins has been decreased for illustration purposes. The values exceeding a predefined acceleration threshold, defined as the typical acceleration occurring during manual transport, are subsequently summed **(C)**. This approach allows the forces acting during transport to be graphically represented as the AUC value for each transport instance **(C)**.

### Diagnostic methods

2.7

#### Point-of-care devices for coagulation diagnosis

2.7.1

A wide range of coagulation tests are available for point-of-care diagnostics, with different manufacturers offering similar test principles, as well as various methods that capture different aspects of coagulation. Among them, viscoelastic testing principles play a prominent role. Essentially, all POC VET devices measure the viscoelastic properties of blood clots formed in whole blood samples. By quantifying the kinetics of clot formation and the strength of the clot, these devices enable the detection and algorithm-driven treatment of coagulation disorders. In the context of the VETaPT trial, various POC hemostasis testing systems are employed. While the viscoelastic testing devices operate on the shared principle of analyzing the clot’s mechanical properties during formation, they differ in technical implementation and the reagents used to initiate coagulation. In contrast, the Multiplate^®^ analyzer is based on a different principle: it measures platelet function by detecting changes in electrical impedance as activated platelets adhere and aggregate on sensor wires. This approach represents a fundamentally different methodology from viscoelastic testing. Owing to the point-of-care nature of all these devices, the results are available at the site of critical care in a timely manner.

#### ClotPro^®^

2.7.2

The ClotPro^®^ (Haemonetics, United States) uses a cuvette with 340 μL of whole blood, where coagulation is initiated by adding coagulation factors. The cuvette is sealed with a plunger. As the measurement begins, the cuvette starts to rotate. The clot that forms between the cuvette and the plunger slows the rotation, creating a resistance that is graphically displayed and output as the clot strength in millimeters. The addition of different agents into the cuvette with coagulation factors changes the results of the ClotPro^®^ test. Currently, nine different test approaches exist for the ClotPro^®^ system, although not all are part of the VETaPT trial. These nine tests are implemented practically via nine different pipette tips, each containing different medication additives, depending on the test. For example, Fib-Test-specific additives inhibit platelet activity, resulting in a clot composed mostly of fibrin, and this test allows for inferences regarding the fibrinogen content of the patient’s blood. The varying test approaches allow for tailored, factor-specific therapy.

#### ROTEM^®^ sigma

2.7.3

The ROTEM^®^ sigma (Werfen TEM Innovations, Munich) consists of a cartridge system that contains the cups and pins for different tests, running simultaneously. In this approach, the cups are stationary while the pins are moved. An optical system detects displacement via a change in the reflection of a laser so that, knowing the applied force, the deceleration can be determined. It is then also graphically displayed and output as the clot strength in millimeters. For ROTEM^®^ sigma, two test cartridges are available, each containing four running tests. The “ROTEM^®^ sigma complete+hep” cartridge includes the following tests: FIBTEM, EXTEM, INTEM, and HEPTEM. The latter inhibits any potential heparin effect. The “ROTEM^®^ sigma complete” cartridge includes the tests FIBTEM, EXTEM, INTEM, and APTEM. The latter detects potential hyperfibrinolysis through the tranexamic acid included in the test.

#### TEG6s^®^ and TEG^®^ PlateletMapping

2.7.4

The TEG6s® system (Haemonetics, United States) is also a cartridge system. The determination of clot thickness is no longer mechanical, as it is based on the delay of a moving component but rather involves the measurement of the resonance frequency of the blood sample, which correlates with the viscoelastic properties of the developing thrombus. A solid clot, for example, has a significantly higher resonance frequency than uncoagulated, liquid whole blood. Since the resonance frequency corresponds to the largest amplitude of mechanical displacement of the clot, the resonance frequency can be determined by its measurement via a diode. The determined frequency is then translated into a VET curve by converting it into a clot thickness, also given in millimeters. TEG® PlateletMapping is a cartridge for the TEG6s® system that includes viscoelastic tests with the platelet activators adenosine diphosphate (ADP) and arachidonic acid (AA). This allows for the calculation of the proportion of drug-inhibited platelets.

#### Multiplate^®^

2.7.5

Multiplate^®^ (Roche Diagnostics, Basel, Switzerland) is a system for platelet aggregometry that electrically measures platelet activation after the addition of the following initiators: ADP, AA, and thrombin receptor-activating peptide 6 (TRAP). The adhesion of activated platelets to the measuring electrodes leads to a change in impedance, which is measured relative to a reference electrode. The use of multiple electrodes allows for internal quality control within each measurement.

The following laboratory, patient, and participant data will be collected as part of the study:
*Conventional laboratory parameters for hemolysis detection:*
Blood count, potassium, lactate dehydrogenase (LDH), aspartate aminotransferase (AST), haptoglobin, hemolysis index
*Conventional laboratory coagulation parameters:*
International normalized ratio (INR), activated partial thromboplastin time (aPTT), thrombin time, fibrinogen
*ClotPro^®^:*

ExTest, InTest, FibTest, tPATest, ECAtest, and RVVtest with the following parameters estimated:

Clotting Time (CT)Clotting Formation Time (CFT)Angle *α*Clot firmness after 5 min (A5)Clot firmness after 10 min (A10)Maximum Clot Firmness (MCF)Maximum Fibrinolysis (ML)Lysis time (LT)
*ROTEM^®^ sigma:*

EXTEM, INTEM, FIBTEM, APTEM – with the following parameters estimated:

Clotting Time (CT)Clotting Formation Time (CFT)Clot firmness after 5 min (A5)Clot firmness after 10 min (A10)Maximum Clot Firmness (MCF)Maximum Fibrinolysis (ML)Lysis time (LT)*TEG6s^®^*:

CK, CKH, CRT, and CFF with the following parameters estimated:Reaction Time (R)Clotting speed (K)AngleMaximum Clot Firmness (MA)Clot Stability (Lyse30)*TEG^®^ PlateletMapping* with the following parameters estimated:Maximum Clot Firmness after Kaolin with Heparinase (HKH-MA)Maximum Clot Firmness after Activator F (ActF-MA)Maximum Clot Firmness after Activator F with Arachidonic Acid (AA-MA)Maximum Clot Firmness after Activator F with ADP (ADP-MA)Percentage of ADP-inhibited platelets (ADP % Inhibition/% Aggregation)Percentage of AA-inhibited platelets (AA % Inhibition/% Aggregation)
*Multiplate^®^:*
ADPtestASPItestTRAPtest
*Demographic and disease-specific data of critically ill septic patients:*

**Table tab1:** 

Date of admission	Date, time
Date of blood collection	Date, time
Date of birth	Date
Height (cm)	Number
Weight (kg)	Number
Gender	m/f/d
Main diagnosis	Text
SAPS-II-Score	Number
APACHE-II-Score	Number
SOFA-Score Zahl	Number
Charleston-Comorbidity-Index	Number

**Table tab2:** 

Comorbidities	
Arterial hypertension	Y/N
Diabetes	Y/N
Obesity	Y/N
Coronary heart disease	Y/N
Chronic arrhythmia	Y/N
Chronic obstructive lung disease	Y/N
Other lung diseases	Y/N
History of venous thrombosis	Y/N
Nicotine abuse	Y/N
History of organ or bone marrow transplant	Y/N
Chronic kidney disease	Y/N
Chronic dialysis	Y/N
Bleeding disorder on admission	Y/N
Thromboembolic complications on admission	Y/N
History of ischemic stroke	Y/N
History of hemorrhagic stroke	Y/N
Acute COVID-19 infection	Y/N
Date of positive COVID test	Date
History of COVID-19-infection	Y/N
Nosocomial infection	Y/N
COVID-19 test on admission	Y/N

